# Whole-body hypothermia in mild neonatal encephalopathy: protocol for a multicentre phase III randomised controlled trial

**DOI:** 10.1186/s12887-024-04935-4

**Published:** 2024-07-18

**Keywords:** Mild encephalopathy, Hypothermia, Magnetic resonance spectroscopy

## Abstract

**Background:**

Mild hypoxic ischemic encephalopathy is associated with sub optimal cognition and learning difficulties at school age. Although whole-body hypothermia reduces death and disability after moderate or severe encephalopathy in high-income countries, the safety and efficacy of hypothermia in mild encephalopathy is not known. The cooling in mild encephalopathy (COMET) trial will examine if whole-body hypothermia improves cognitive development of neonates with mild encephalopathy.

**Methods:**

The COMET trial is a phase III multicentre open label two-arm randomised controlled trial with masked outcome assessments. A total of 426 neonates with mild encephalopathy will be recruited from 50 to 60 NHS hospitals over 2 ½ years following parental consent. The neonates will be randomised to 72 h of whole-body hypothermia (33.5 *±* 0.5 C) or normothermia (37.0 *±* 0.5 C) within six hours or age. Prior to the recruitment front line clinical staff will be trained and certified on expanded modified Sarnat staging for encephalopathy. The neurological assessment of all screened and recruited cases will be video recorded and centrally assessed for quality assurance. If recruitment occurs at a non-cooling centre, neonates in both arms will be transferred to a cooling centre for continued care, after randomisation. All neonates will have continuous amplitude integrated electroencephalography (aEEG) at least for the first 48 h to monitor for seizures. Predefined safety outcomes will be documented, and data collected to assess resource utilization of health care. A central team masked to trial group allocation will assess neurodevelopmental outcomes at 2 years of age. The primary outcome is mean difference in composite cognitive scores on Bayley scales of Infant and Toddler development 4th Edition.

**Discussion:**

The COMET trial will establish the safety and efficacy of whole-body hypothermia for mild hypoxic ischaemic encephalopathy and inform national and international guidelines in high income countries. It will also provide an economic assessment of whole-body hypothermia therapy for mild encephalopathy in the NHS on cost-effectiveness grounds.

**Trial registration number:**

NCT05889507 June 5, 2023.

## Introduction

Mild hypoxic ischemic encephalopathy (HIE) occurs in around 0.8 to 1 per 1000 livebirths [1]. In the UK approximately 1400 babies are admitted to neonatal units with HIE every year; of these around 600 have moderate or severe HIE and 800 have mild HIE [1].

Although in high income countries, neonates with mild HIE are unlikely to die or develop major neurodisability [2], careful long term follow-up studies have reported cognitive deficits that becomes apparent by 2 years and possibly increase with age. Finder et al. reported that the mean (SD) Bayley-III Cognitive Scale score of 55 un-cooled babies with mild HIE was 6 points lower than 152 healthy peers (98 [12] versus 104 [15]) [2] when assessed between 18 and 42 months of age, although only 68% could be assessed. Murray et al. reported mean IQ of 22 babies with mild HIE was 18 points lower than 30 healthy peers (99 versus 117; *p* < 0.001) at 5 years of age [3]. Moreover, 38% of children with mild HIE had special educational needs compared with 18% of their siblings and 0% of healthy peers [4]. The PRIME (Prospective Research in Mild Encephalopathy) study recruited 63 un-cooled babies with mild HIE from Canada, US, UK, and Thailand, of which 43 (68%) were assessed at 2 years; Seven (16%) had a Bayley Cognitive Scale Composite score of less than 85 points [5], indicating at least mild cognitive impairment. Given the higher occurrence of mild HIE, health and economic burden at a population level is likely to be substantial [6].

Whole-body hypothermia, an evidence-based therapy for babies with moderate or severe encephalopathy in high income countries [7], is increasingly used for babies with mild HIE without an adequate evaluation of safety and efficacy [8, 9]. In the UK, around 30% of the 3511 babies with mild hypoxic ischaemic encephalopathy admitted to neonatal units between 2011 and 2016 received whole-body hypothermia. During the same period, 830 neonates without encephalopathy were also cooled. Furthermore, the number of babies with moderate encephalopathy doubled from 141 to 293 indicating many neonates with mild HIE might have been misclassified as moderate HIE [10].

Separately, a London neonatal transport audit reported that of the 170 babies transported for whole-body hypothermia between 2017 and 2019, 45% had mild HIE or birth acidosis without encephalopathy and did not meet the current criteria for whole-body hypothermia [11].A structured neurological examination to determine severity of HIE prior to initiation of whole-body hypothermia was either not performed or not documented in most babies [11].

Short term outcomes on 7181 babies with mild HIE are available from the Canadian (*n* = 1089; cooled 36%) [12], Californian (*n* = 1364; cooled 71%) [13], Children’s Hospital Neonatal Consortium (*n* = 272; cooled 95%) [14]; US Children’s Hospitals National Database (*n* = 945; cooled 13%) [15] and the UK (*n* = 3511; cooled 30%) [16] registries. These data show that whole-body hypothermia significantly increased duration of ventilatory support (2 days versus 1 day), intensive care stay (9 days versus 6 days), need for invasive ventilation (60% versus 45%), use of opioid infusion (67% versus 12%), disseminated intravascular coagulation (8% versus 2%), hepatic dysfunction (23% versus 11%), cardiac dysfunction (8% versus 2%), discharge home on oxygen (26% vs. 15%) and tube feeding at hospital discharge (22% versus 13%) compared to usual care. Other adverse short-term outcomes noted only in babies with mild HIE who underwent whole-body hypothermia include hypotension (16%), thrombocytopenia (10%), coagulopathy (17%), persistent metabolic acidosis (8%), and subcutaneous fat necrosis (1%). No neurodevelopmental outcome data are available from any of these registries, so the long-term impact is unknown.

A well-designed observational study (COOL Prime Study: Comparative Effectiveness for Cooling Prospectively Infants with Mild Encephalopathy) evaluating the neurological outcomes of 430 neonates with mild HIE from 15 hospitals is currently ongoing in the USA (NCT04621279). However, in the absence of a randomised controlled arm, no conclusions about safety and efficacy of whole-body hypothermia can be made from observational data [17].

Lack of hypothermic neuroprotection and potential harms reported in two recent major hypothermia trials [18, 19] have highlighted the hazards of therapeutic drift, and the critical importance of conducting clinical trials before extending its use to untested populations. The first of these trials involved 408 neonates with moderate or severe HIE from low and middle-income countries (HELIX; Hypothermia for Encephalopathy in low and middle-income countries) [19], which reported a significant increase in mortality with whole-body hypothermia. The second trial (Preemie Hypothermia trial) included 151 premature neonates with moderate or severe HIE born between 33 + 0 to 35 + 5 weeks and reported that whole-body hypothermia increased the probably of death by 77% [18]. Unlike the original hypothermia trials where hyperthermia occurred in 14–29% of the control arms [20–22], both HELIX trial [19] and PREMIE hypothermia trials had much lower occurrence of hyperthermia in the control arm.

The British Association of Perinatal Medicine (BAPM) [23] and the American Academy of Pediatrics [16, 24, 25] have called for an urgent clinical trial to assess safety and efficacy of hypothermia for mild HIE.

### Aims

To examine if whole-body hypothermia to 33.5 *±* 0.5 °C, initiated within six hours of birth and continued for 72 h, improves cognitive development at two years of age after mild neonatal encephalopathy when compared with normothermia at 37.0 *±* 0.5^0^C.To examine if a prospective trial-based economic evaluation supports the provision of whole-body hypothermia therapy for mild HIE in the NHS on cost-effectiveness grounds.

## Study design

### Setting

Cooling in mild encephalopathy (COMET) is a phase III multi-centre open label two-arm randomised controlled trial (RCT) with internal pilot and masked outcome assessments. Administration of cooling therapy cannot be masked. The trial will recruit from five neonatal operational delivery networks (ODN) involving around 50 to 60 NHS hospitals. The recruitment will occur at both tertiary and non-tertiary (non-cooling) centres, although the neonates recruited from non-tertiary centres will be transferred to a tertiary centre after randomisation.

### Patient identification and screening

All babies born at or after 36 weeks of gestation and requiring prolonged resuscitation at birth (defined as continued resuscitation at 10 min after birth or 10-minute Apgar score less than 6) or those with severe birth acidosis (defined as any occurrence of: pH less than 7.00 or base deficit *≥* 16mmol/l in the cord or baby’s gas sample within 60 min of birth) and admitted to the neonatal unit will be screened for eligibility.

All neonates meeting the screening criteria will have a neurological examination using expanded modified Sarnat staging by a trained and certified examiner at the time of admission and after one hour of age. The expanded modified Sarnat staging has additional criteria for diagnosis of neonates with mild HIE. A video recording (around 5 to 10 min) of this examination will be obtained in all cases.

Parental consent to use this video recording for research and transfer to the central team at Imperial College for quality assurance will be obtained at a later stage. If parental consent is denied, then the videos will be deleted. Babies with an abnormal neurological assessment will be started on continuous aEEG monitoring and will be recruited if they meet the trial inclusion criteria.

### Inclusion criteria

All babies born at or after 36 weeks of gestation with a birth weight of 1800 g or more with birth acidosis or requiring resuscitation at birth will be screened for eligibility. Parents will be approached for consent if the baby meets all the three (A + B + C) criteria below:

A)Evidence of intra-partum hypoxia-ischemia defined as any of: Apgar score of less than six at 10 min after birth or continued need for resuscitation at 10 min after birth or severe birth acidosis defined as any occurrence of: pH less than 7.0 or Base deficit *≥* 16mmol/l in a cord or baby gas sample within 60 min of birth.B)Evidence of mild HIE defined as: two or more abnormal findings in any of the six categories of the expanded modified Sarnat examination (level of consciousness, spontaneous activity, posture, tone, primitive reflexes, and autonomic nervous system) but not meeting the diagnosis of moderate or severe HIE on a standardised examination performed by a certified examiner between 1 and 6 h of age.C)Normal amplitude, with or without sleep wave cycling, on the aEEG performed for at least 30 min between 1 and 6 h of age. Normal amplitude will be defined as upper margin of the aEEG activity more than 10 microvolts and the lower margin more than 5 microvolts on a single channel aEEG.

### Exclusion criteria

Neonates who meet the BAPM criteria for whole-body hypothermia for moderate/severe HIE.Neonates without encephalopathy defined as less than two abnormalities on structured neurological examination.Neonates with major congenital or chromosomal anomalies identified prior to randomisation.Neonates with birthweight less than 1800 g or gestational age less than 36 weeks at birth.Neonates who received muscle relaxation, or anti-seizure medications prior to neurological assessment that impacts the neurological examination.Neonates with moderate or severe background voltage abnormalities or seizures on aEEG.Neonates already enrolled in interventional studies.

### Randomisation and trial intervention

If the neonate meets the trial inclusion criteria, the availability of a cooling device and intensive care cot space at a cooling centre will be checked before approaching parents for trial participation. Once parental consent is obtained, babies will be randomised to whole-body hypothermia or normothermia within 6 h of birth, using a web-based program developed by Sealed Envelope private limited, London. The randomisation will be performed using minimisation to balance the treatment allocation by site and severity of encephalopathy within mild encephalopathy.

Initial assessment and randomisation (and initiation of whole-body hypothermia or normothermia) will occur at the hospital of birth. The babies in both arms, who are born at a non-cooling centre (Local Neonatal Unit (LNU) or Special Care Baby Unit (SCBU)) will be then transferred to the nearest neonatal intensive care (NICU) cooling centre for continued care.

### Whole body hypothermia (intervention group)

Whole-body hypothermia (33.5 *±* 0.5 °C) will be initiated within 6 h of birth and continued for 72 h using a servo-controlled cooling machine at the hospital of birth. Neonates born at a non-cooling centre will be transferred to an NICU cooling centre for continued care. Passive cooling methods will not be allowed. After 72 h of whole-body hypothermia at 33.5 *±* 0.5 °C, the baby will be rewarmed at 0.5 °C per hour to reach 37.0 *±* 0.5 °C over 6 to 8 h.

### Normothermia (Control group)

The rectal temperature will be maintained at 37 *±* 0.5 °C using servo-controlled incubators with specific attention to temperature management for preventing iatrogenic hyperthermia. Rectal temperature will be recorded, as in the whole-body hypothermia group.

Babies in the control group who develop seizures and progress to moderate HIE between 6 and 24 h may be treated with whole-body cooling for 72 h as clinical care, at the discretion of the clinical team. It is estimated that around 5% of the neonates in both groups may develop seizures after 6 h of age.

### Sedation

Pre-emptive use of narcotic infusions, a common practice during whole-body hypothermia, is often a major concern for parents. Secondary analysis of the NICHD Neonatal Research Network hypothermia trial and the Magnetic Resonance Biomarkers in Neonatal encephalopathy (MARBLE) study have reported opioid sedation increased hospital stay and duration of ventilation and had no neurodevelopmental benefits [26–29]. Hence, use of pre-emptive sedation during whole-body hypothermia will be minimised unless the neonate is distressed with persistent tachycardia and with documentation of pain (NPASS) scores.

### Monitoring and care in both groups

Babies with breathing difficulties or apnoea will have appropriate support with non-invasive (CPAP/high flow) or invasive ventilation. All babies will have continuous aEEG monitoring (minimum one channel; 3 electrodes) for at least 48 h after birth. Continuous monitoring using aEEG for the first 88 h is the current standard care for babies undergoing whole-body hypothermia in the NHS. All neonates will have monitoring of physiological and laboratory parameters as clinically indicated. Enteral milk feeds will be administered in both groups and increased as tolerated as per local unit protocols.

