### Secondary outcomes

Outcomes assessed during neonatal hospitalisation:

Seizures (clinical and aEEG confirmed).Duration of intensive care defined as number of days of neonatal intensive care.Duration of hospital stay defined as the total number of days of inpatient care in a neonatal unit.Duration of mechanical ventilation defined as number of hours on invasive ventilation through an endotracheal tube.Duration of inotropic support defined as total number of hours on inotropic support.Bloodstream or cerebrospinal fluid positive infection defined as isolation of a pathogenic organism from blood or cerebrospinal fluid along with a clinical diagnosis of sepsis, at any time during neonatal hospitalisation.Thrombocytopenia or coagulopathy requiring transfusion of blood products.Successful breastfeeding (at hospital discharge).Brain injury scores on conventional magnetic resonance imaging.

Longer term secondary outcomes assessed at 24 (*±* 2) months include:

Survival without any neurological impairment defined as a score of *≥* 85 in all Bayley-IV domains (motor, language, and cognitive), normal neurological examination with no cerebral palsy (Gross motor function classification system score 0), no hearing or visual impairment (as reported by parents), and no seizure disorder.Preschool Child Behaviour Checklist (CBCL 1½-5) will be completed by parents at the 24(*±* 2) month assessment to provide a standardised measure of children’s behavioural outcomes on scales that assess internalizing and externalizing behaviour problems and a Total Problems Scale. Mean standardised T-scores on each scale will be compared between groups. The CBCL checklist will be completed after the Bayley IV assessments.Cerebral palsy with a gross motor function classification system score (GMFCS) of 2 or more.Head circumference of less than 2 standard deviations.

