### Statistics and data analysis

The primary outcome is the Cognitive Scale Composite score from the Bayley-IV examination at 24(*±* 2) months. Based on previous experience the scores are expected to be approximately normally distributed, and thus a two-sample t-test will be used to compare between groups. The mean difference in outcome between groups will be reported, along with a corresponding confidence interval. If the outcome scores are not normally distributed, an appropriate data transformation will be explored, or alternatively a non-parametric test (Mann-Whitney test) may be utilised.

Secondary outcomes are both short term (in hospital) or longer term (at 24 months). Continuous secondary outcomes will be analysed using the unpaired t-test if normally distributed, or the Mann-Whitney otherwise. The Chi-square test or Fisher’s exact test will be used to compare categorical outcomes between groups. For each outcome, a point-estimate of difference between groups will be reported, alongside a corresponding confidence interval.

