## Discussion

We describe the protocol of the COMET trial, a phase III randomised controlled trial of whole-body hypothermia mild encephalopathy. The COMET trial will establish the safety and efficacy of whole-body hypothermia for mild HIE, inform national and international guidelines, and will establish uniform practice across the NHS and other high-income countries. It will also provide an economic case for the NHS, if whole-body hypothermia is beneficial. Alternatively, whole-body hypothermia treatment will be discontinued for babies with mild HIE if it is found to be ineffective or unsafe, again leading to cost savings. In the absence of a clinical trial, whole-body hypothermia will be increasingly used for this population, and safety and efficacy will remain unknown. An additional downstream effect of the COMET trial is a national standardisation of neurological assessment based on expanded modified Sarnat Staging.

The COMET trial design was informed by a COMET pilot randomised controlled trial data and extensive discussion with parents of babies with mild HIE [35]. A total of 101 neonates with mild HIE from six tertiary neonatal intensive care units in the UK and Italy were recruited in the COMET pilot trial over 3 ½ years. The neonates were randomised based on the age at randomisation. Those aged less than 6 h at the time of recruitment were randomised to either normothermia or therapeutic hypothermia for 72 h at 33.5 °C (early randomisation cohort). The neonates with mild HIE who were already started on therapeutic hypothermia as part of clinical care were randomised to either rewarming at 48–72 h of age (late randomisation cohort). Although the injury scores on conventional MR were similar across the groups, the mean (SD) [NAA] level was higher in the normothermic group compared with 48 h and 72-hour hypothermia groups. Seizures after six hours of birth occurred in 2.9%, 3.2% and 5.5% of the normothermic, 48 h and 72-h hypothermia groups [35].

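### aEEG time may differ by arm (48 h guaranteed to all, 88 h usual for cooled babies), so the whole-stay seizure comparison may be biased towards more seizures with cooling

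*Protocol article*

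**What the plan says.** Four statements in the protocol article bear on this point.

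- **Monitoring.** Under Monitoring and care in both groups: "All babies will have continuous aEEG monitoring (minimum one channel; 3 electrodes) for at least 48 h after birth". The next sentence reads: "Continuous monitoring using aEEG for the first 88 h is the current standard care for babies undergoing whole-body hypothermia in the NHS". No usual duration is given for babies kept at normothermia. The abstract gives the purpose of the monitoring: "at least for the first 48 h to monitor for seizures".
- **Outcome.** Under Secondary outcomes, the first item assessed during neonatal hospitalisation is "Seizures (clinical and aEEG confirmed", closed by a bracket and with no time limit.
- **Analysis.** Under Statistics and data analysis: "The Chi-square test or Fisher’s exact test will be used to compare categorical outcomes between groups". The section on recording and reporting of adverse events adds that safety monitoring will draw on the secondary outcomes.
- **Masking and expected rate.** Under Setting: "Administration of cooling therapy cannot be masked". Under Normothermia (Control group): "It is estimated that around 5% of the neonates in both groups may develop seizures after 6 h of age".

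**The concern.** An outcome that depends on a monitor can be compared fairly only if the monitor runs for similar lengths of time in both arms. Here the guaranteed time is 48 h and the usual time for a cooled baby is 88 h. Staff know the allocation, so the length of recording can follow it.

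A control whose aEEG is removed at 48 h could still have a later seizure that goes unrecorded, while the same seizure in a cooled baby would be seen. Such losses lower the control count only, so the artefact runs against cooling. The outcome feeds the safety assessment and few events are expected. A handful of missed cases could therefore shift the reported estimate, and readers could not tell a detection effect from a treatment effect.

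**Working it through.** **The plan's own figures.** The article gives no sample size, power or expected difference for seizures. Its primary-outcome calculation does reproduce: a 5-point difference, SD 15, two-sided 0.05 and 90% power by t-test give 191 per arm, and 191/0.9 rounds up to 213 per arm, or 426. Nothing below alters that.

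**Inputs from the article**
- Guaranteed aEEG: 48 h. Usual aEEG for cooled babies: 88 h. Possible gap: 88 − 48 = 40 h, which is 40/88 = 45% of the longer window.
- Expected seizure rate after 6 h of age: 5% in both groups.
- Babies per arm: 426/2 = 213, so expected cases per arm are 213 × 0.05 = 10.65, about 10.7.
- Cooling starts within 6 h of birth, lasts 72 h and is followed by 6 to 8 h of rewarming. It can end as late as 6 + 72 + 8 = 86 h. All of rewarming falls after 48 h.

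**Inputs that are assumptions** (the article does not give them)
- s: the share of seizing babies whose first seizure comes after 48 h.
- c: the share of those late cases still detected in controls, for example because a clinical sign prompts aEEG. All late cases in cooled babies are taken as detected.

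**Formulas.** With no true effect:
- Observed control rate = 5% × (1 − s(1 − c)).
- Apparent risk ratio = 1/(1 − s(1 − c)).
- Missed control cases = 10.65 × s(1 − c).

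| s | c | Control rate | Spurious excess (points) | Apparent risk ratio | Missed control cases | Chance of a significant excess with cooling |
|---|---|---|---|---|---|---|
| 0 | any | 5.0% | 0 | 1.00 | 0 | 2.5% (nominal) |
| 10% | 0 | 4.5% | 0.5 | 1.11 | 1.1 | 4% |
| 20% | 0 | 4.0% | 1.0 | 1.25 | 2.1 | 7% |
| 30% | 0 | 3.5% | 1.5 | 1.43 | 3.2 | 12% |
| 40% | 0 | 3.0% | 2.0 | 1.67 | 4.3 | 18% |
| 50% | 0 | 2.5% | 2.5 | 2.00 | 5.3 | 27% |
| 20% | 0.5 | 4.5% | 0.5 | 1.11 | 1.1 | 4% |
| 40% | 0.5 | 4.0% | 1.0 | 1.25 | 2.1 | 7% |

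The last column uses the normal approximation to a two-sided 5% test of two proportions with 213 per arm, counting only an excess in the cooled arm. For s = 40% and c = 0:
- The mean rate is 4%, so the null standard error is √(0.04 × 0.96 × 2/213) = 0.0190.
- The standard error under the two rates is √((0.05 × 0.95 + 0.03 × 0.97)/213) = 0.0190.
- The chance is Φ((0.02 − 1.96 × 0.0190)/0.0190) = Φ(−0.91) = 18%.

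The 50% row lies outside the range used in the conclusion. It is shown because seizures spread evenly from 6 to 88 h would give s = 40/82 = 49%.

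**With a common window to 48 h.** Both arms are then counted over time that is monitored in both. The artefact from unequal recording length is zero by construction, whatever s and c are.

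**The case against.** The strongest objection is that the article does not say controls come off aEEG at 48 h. That figure is a minimum, set under a heading covering both groups. The 88 h figure describes NHS practice and is not an instruction for one arm. Babies in both arms are cared for in cooling centres, where longer recording may be routine. This stands: unequal monitoring is allowed by the plan, not prescribed.

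The outcome wording is also ambiguous. If clinical seizures count on their own, late events remain countable in both arms. If both elements are required, purely electrographic late seizures would not count in either arm, and a clinical sign could lead to aEEG being restarted. Either reading shrinks the artefact. But if aEEG confirmation is required, a control who stays off aEEG cannot be counted, so the ambiguity does not remove it.

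A reader might infer that cooling is bound to look as if it causes more seizures, and might cite the pilot: "Seizures after six hours of birth occurred in 2.9%, 3.2% and 5.5% of the normothermic, 48 h and 72-h hypothermia groups". The article does not support that. It gives no seizure timing, a true effect of cooling could add to or offset the artefact, and the pilot pattern fits either explanation.

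It can also be said that outcome definitions belong in the manual of procedures, which the article promises. That would answer a complaint about missing detail. Here, however, what the article does state (a 48 h floor, a longer norm for one arm and a whole-stay comparison) already permits unequal detection.

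Finally, stopping the only comparison at 48 h would exclude late cooling and all of rewarming, when a real treatment-related seizure could occur. This stands, and it shapes the fix.

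**Conclusion.** The point holds as a risk of bias, not a certainty. As written, the plan lets aEEG time differ by arm and compares seizures over the whole stay without a common window. The detection artefact, if present, runs towards more seizures with cooling.

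Its size cannot be known from the article. At 5% in both arms, with 10% to 40% of first seizures after 48 h and all of these missed in controls, the apparent risk ratio is 1.11 to 1.67. If half the late control seizures are still detected, the range falls to 1.05 (1/0.95) to 1.25. The late share and the completeness of the loss are both assumptions. A falsely significant result is unlikely unless many seizures come late; the likelier harm is a distorted estimate based on about ten events per arm.

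One secondary outcome, which also informs safety, is affected. The primary outcome and sample size are not.

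**What to change.** 1. Add a between-arm comparison of aEEG-confirmed seizures from randomisation to 48 h of age, the window guaranteed in both arms, and name it as the analysis free of unequal recording length.
2. Keep and report whole-stay seizures by arm beside it, including those after 48 h and around rewarming, with a stated caution on unequal detection.
3. Record hours of aEEG per baby and report them by arm, so that readers can judge how far monitoring differed.
4. Say whether a seizure counts on clinical grounds alone, on aEEG alone, or only when both are present.

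The cost is one extra recorded variable, one extra analysis and some outcome wording; clinical monitoring does not change. The 48 h comparison will have fewer events and does not cover rewarming, which is why the whole-stay result must stay beside it. Recording of aEEG hours should start early, because they may be hard to recover afterwards.
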